### Trial design

The SPPA trial is designed as a multicenter assessor-blinded, controlled, randomized, superiority, pragmatic trial to assess the effectiveness of daily SMS reminders of antihypertensive medication provided by pharmacists in addition to sPhC compared with sPhC only. Patients will be individually randomized into two parallel groups in a 1:1 allocation ratio. Participants in the intervention group will receive daily SMS reminders of medication intake, whereas participants in the control group will receive sPhC only. The trial will last three months with a recruitment period of two months. The Standard Protocol Items: Recommendations for Interventional Trials (SPIRIT) checklist for study protocols [63] is provided in Additional file 1. Details about the pragmatic design of the SPPA trial are provided in the PRagmatic Explanatory Continuum Indicator Summary (PRECIS-2) table of scores for trial domains and the PRECIS-2 wheel scheme [64] in Additional file 2.

### Trial setting

The SPPA trial will be conducted in six or more community pharmacies in the Slovak Republic located in all main Slovak regions. Furthermore, half of the pharmacies will be selected from rural and half from urban regions. This selection process will ensure better generalizability and high external validity of trial results for the Slovak population of older hypertensive patients.

### Study population

Trial population consists of hypertensive ambulatory patients aged 55 years or older who are taking antihypertensive medication for at least one year without any discontinuation. Based on the trials’ pragmatic design, eligibility criteria are liberal and can be assessed solely using the information available to the pharmacists.

### Inclusion criteria

Age ≥ 55 years (from the day of the 55th birthday inclusive);Diagnosis of primary hypertension (I10 according to ICD-10 [65]);Filling of antihypertensive prescription(s) at trial recruitment (Visit 1);Duration of antihypertensive drug treatment for at least one year without any discontinuation;Ownership of a mobile phone for personal use with the ability to open and read SMS;Understanding of Slovak language on native-speaker level;Informed consent for participation in the clinical trial and personally signed informed consent form.

### Exclusion criteria

Exclusion criteria assessed prior to patient enrolment:Planned hospitalization during the trial period;Biological impairment affecting the ability to read the SMS (e.g. loss of vision, visual field cuts, aphasia);Living in the same household with another trial participant;Participation in another clinical trial.

Exclusion criteria assessed after patient enrolment:Hospitalization during the trial period;Patient informs he/she will not be able to participate in the trial;Withdrawal of informed consent.

We have strived to maintain broad eligibility criteria to ensure our trial population best reflects the real-world population of patients for whom the intervention is intended. Nevertheless, we accepted some inclusion and exclusion criteria, which can strengthen the validity of the trial’s results while not introducing selection bias. We focus on patients with primary hypertension to limit the confounding influence of secondary hypertension causes both on patients’ adherence to medication and resulting blood pressure control. Patients with other co-morbidities are eligible to participate in the study. We will recruit patients while filing their prescription at the trial pharmacy. According to Slovak health legislation, physicians are allowed to prescribe medication to chronic patients for a maximum of three months. Hence, patients who are collecting their medicines at the day of the recruitment will in most cases begin to take the pills out of the collected medication package on the next day (first day of the intervention), enabling the precise calculation of pill count rates. Furthermore, chronic patients in Slovakia visit the pharmacy usually in three-month cycles. We will include only patients who take their antihypertensive medication for at least one year because these patients are considered to have reached their acceptance phase of medicinal treatment and consequently are at lower risk of early therapy discontinuation due to non-acceptance [66]. Trial participants hospitalized during the trial will be excluded since during their hospital stay healthcare providers will manage their medication resulting in the redundancy of SMS reminders.

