### Randomization, allocation, and concealment

Participants will be randomly assigned to either control or intervention group with a 1:1 allocation ratio. The external unblinded trial pharmacist will generate a simple randomization and allocation list with randomization numbers (patient trial codes) stratified by gender for each trial center. Freely available online software, Research Randomizer, will be used for this purpose [73]. The external unblinded trial pharmacist will provide each trial pharmacy with equal number of sequentially numbered, opaque, sealed randomization envelopes for male (blue) and female participants (red). Trial pharmacists will recruit patients in the natural, unpredictable order as they enter the pharmacy and agree to participate in the trial. After signing the informed consent form, trial pharmacists will assign a patient trial code to each participant from a randomization envelope selected in ascending order.

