### Statistical analysis

We will conduct all analyses according to the intention-to-treat principle, striving to collect data from all participants. In case of missing data, data imputation techniques (multivariate imputation via chained equations) will be used. Predictive mean matching and logistic regression [86] will be used for continuous (e.g. systolic blood pressure) and categorical (e.g. MMAS-8) variables, respectively. For comparison, a per-protocol analysis will also be carried out. We will comprehensively report all missing data along with the reasons why these data are missing and explore their patterns. This information will help us to appropriately adjust future study protocols. No interim analysis is planned. Descriptive statistics will be reported as means (SD) or medians (interquartile range) for continuous variables and proportions for categorical variables. All statistical analyses will be carried out with a 5% type I error rate.

Results of the SPPA trial will be reported following the Consolidated Standards of Reporting Trials (CONSORT) 2010 statement [87, 88] and the Guidelines for reporting of health interventions using mobile phones: mobile health (mHealth) evidence reporting and assessment (mERA) checklist [36]. All analyses will be conducted with R software [89] using the basic statistical functions as well as robust functions from the package WRS2 [90] and for plotting and graphs the ggplot2 package [91].

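### Randomised participants are to be excluded after enrolment for hospitalisation, inability to continue or withdrawal, which as worded conflicts with intention-to-treat for all analyses

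*Protocol article*

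**What the plan says.** The protocol article, under Exclusion criteria, has a second list: "Exclusion criteria assessed after patient enrolment:Hospitalization during the trial period;Patient informs he/she will not be able to participate in the trial;Withdrawal of informed consent". The text below it repeats the first item as a firm rule: "Trial participants hospitalized during the trial will be excluded since during their hospital stay healthcare providers will manage their medication". The reason given is that the reminders become redundant during a hospital stay. The same section describes the eligibility criteria as ones "which can strengthen the validity of the trial’s results while not introducing selection bias".

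Under Randomization, allocation, and concealment: "After signing the informed consent form, trial pharmacists will assign a patient trial code to each participant from a randomization envelope selected in ascending order". A participant is therefore allocated at enrolment, before any of the listed events can occur.

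Under Statistical analysis: "We will conduct all analyses according to the intention-to-treat principle, striving to collect data from all participants". The same paragraph adds "In case of missing data, data imputation techniques (multivariate imputation via chained equations) will be used" and "For comparison, a per-protocol analysis will also be carried out". Under Participant timeline, people who cannot attend the follow-up visit are asked for the pill count, the MMAS-8 and the satisfaction questionnaire by phone.

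**The concern.** An exclusion criterion applied after randomisation ordinarily takes a person out of the trial population. Intention-to-treat keeps that person in the allocated arm. The article states both rules and does not say which governs the primary analysis.

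The listed events need not be independent of outcome or arm. The Background section itself links poor adherence to uncontrolled blood pressure and hospitalisation, so removing hospitalised people may condition on a consequence of the outcome. The Blinding section says that participants know their allocation, and only one arm receives daily messages, so willingness to continue can differ between arms. The assurance about selection bias can be defended for criteria applied before allocation. It cannot be guaranteed for criteria applied afterwards.

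At stake is the denominator of the primary proportion in each arm.

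**Working it through.** **1. The passages side by side**

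| Question | Exclusion criteria | Statistical analysis |
|---|---|---|
| Who is affected? | Hospitalised, unable to participate, consent withdrawn | All participants |
| What happens to them? | Excluded | Analysed by intention-to-treat, missing data imputed |
| Limited to per-protocol? | Not stated | A per-protocol analysis is planned, but not tied to these events |

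No section says that people excluded under the first column are followed up, imputed or kept in the intention-to-treat set. The phone route covers those unable to attend Visit 2. Someone who reports being unable to take part could fall under either rule.

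**2. The plan's own figure**

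Inputs from Sample size calculation: w = 0.2, power 0.9, alpha 0.05, 264 evaluable, about 10% attrition, 300 enrolled.

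- N = (1.960 + 1.282)² / 0.2² = 262.7, so 263, or 264 for equal arms. Power at 264 is 0.901. The stated 264 reproduces.
- 264 / 0.90 = 293.3, so 294 for equal arms. The planned 300 covers this.
- Power at w = 0.2 is 0.934 with all 300 analysed and 0.908 with 270.

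The sample size is not in question. The issue is who is compared.

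**3. Illustration of the possible bias**

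From the plan: 30% adherence in the control group and 150 per arm. Assumed, because the article gives no figures: no true effect (30% in both arms), exclusions in one arm only, a share e of that arm excluded, and a share q of the excluded being adherent.

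- Proportion among those left: p' = (0.30 − e·q) / (1 − e)
- Shift: p' − 0.30
- Standard error: √[p'(1 − p') / (150(1 − e)) + 0.30 × 0.70 / 150]
- With z = shift / SE, two-sided rejection rate ≈ 1 − Φ(1.96 − z) + Φ(−1.96 − z)

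Worked case, e = 0.10 and q = 0: p' = 0.30 / 0.90 = 0.333. SE = √(0.001646 + 0.001400) = 0.0552. z = 0.0333 / 0.0552 = 0.604. The rejection rate is 0.0875 + 0.0052 = 0.093.

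| Excluded in one arm | Excluded who are adherent | Shift (points) | Rejection rate, nominal 5% |
|---|---|---|---|
| 3% | 0% | 0.9 | 5.3% |
| 5% | 0% | 1.6 | 6.0% |
| 10% | 0% | 3.3 | 9.3% |
| 3% | 15% | 0.5 | 5.1% |
| 5% | 15% | 0.8 | 5.3% |
| 10% | 15% | 1.7 | 6.1% |

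The shift favours whichever arm loses the people. Exclusions from the SMS arm favour the intervention, and exclusions from the control arm work against it.

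**4. Balanced exclusions**

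If both arms lose the same share, with the same adherence among those lost, the difference is divided by (1 − e). A null difference stays at zero. The planned 30% versus 49% (19 points) becomes 19 / 0.95 = 20.0 points at 5% excluded and 19 / 0.90 = 21.1 points at 10%.

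**The case against.** The best defence is that the Exclusion criteria section is about taking part, not about analysis. Its stated reason is that reminders are redundant in hospital, and it names no analysis set. The section that governs analysis commits to intention-to-treat, imputation, full reporting of missing data with reasons, and a separate per-protocol analysis. A coherent reading follows: these people stop, their Visit 2 values are imputed, and only the per-protocol set omits them. The article also condenses a fuller protocol that is not shown.

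Much of this stands. A reader might infer that the two rules are irreconcilable, or that excluded people are absent from the data and so cannot be imputed. The documents support neither inference. MMAS-8, blood pressure and sociodemographic data are collected at Visit 1, forms go to the research office monthly, and nothing says that these records are deleted.

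Other points also limit the concern. Planned hospitalisation is screened out before enrolment, the phone route recovers some outcomes, and reasons for discontinuation are collected, so an imbalance could be seen.

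What the defence does not supply is a sentence saying that these people remain in the intention-to-treat set. The coherent reading has to be assumed against a rule that says they are excluded. This is a conflict between two stated rules, not a detail left to another document.

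**Conclusion.** The conflict in wording is real. Followed literally, the rule removes randomised people on events that may depend on adherence and on known allocation.

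Whether bias would result depends on how the rule is applied, and its size cannot be derived from the article. The range of about 0.9 to 3.3 points, with a rejection rate of about 5.3% to 9.3%, rests on three assumptions: no true effect at 30% adherence, 3% to 10% excluded from one arm only, and all of them non-adherent. It shrinks if exclusions are few, balanced or partly adherent. For scale, the plan allows about 10% for attrition of every kind, and the earlier studies it cites lost 3.2% to 19.0%. None of these is a rate for the listed events.

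A reader might also infer that the bias favours the SMS arm, through people tiring of daily messages. The documents do not establish this. If reminders improve adherence and poor adherence leads to hospitalisation, the control arm would lose more people and the bias would run against the intervention. Controls, who know that they receive no reminders, may also leave.

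Withdrawal of consent stands apart, because it can legitimately end data collection. The point does not depend on it.

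**What to change.** - Reword the three post-enrolment items as reasons for stopping participation or follow-up, not for exclusion from analysis. Limit the statement about selection bias to the criteria applied before enrolment.
- State that all randomised participants are analysed in the arm to which they were allocated.
- Seek MMAS-8 and pill count at Visit 2 from these participants where consent allows, using the phone route under Participant timeline.
- For inpatient days when the hospital supplied the medication, adjust the number of pills that should have been taken from the trial package (the denominator of the adherence rate). A package count cannot date individual pills, so the numerator stays as counted.
- Impute the remaining outcomes by the planned chained equations, using data collected before withdrawal as far as consent permits.
- Apply these exclusions only in the per-protocol analysis.

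Whether messages continue during a hospital stay is a separate matter for the sponsor. The cost is a wording amendment and a few extra phone calls, with no additional patients. Because the trial is recruiting, the change should be made before database lock.

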### Trial groups

#### Control group

Participants in the control group will receive sPhC according to the principles of Good Pharmaceutical Practice and national Slovak legislation requirements [53, 54, 67, 68] only. Trial pharmacists will provide the sPhC to the patients while dispensing their medicines at the trial pharmacy. Participants in the control group will also receive a welcome SMS one day after enrolment and an end-of-trial SMS three months after the enrolment (Table 1).

**Table 1 Tab1:** SMS messages in the SPPA clinical trial

SMS	Time of receipt	Content of the SMS
Welcome SMS	Day after enrolment	“Welcome in the SPPA trial. We would like to thank you for participating in this clinical trial. Your participation might help to improve health of other patients as well as the Slovak health care system. Your SPPA trial research team.”
Sample SMS reminder (intervention group only)	Daily for 3 months; starting the day after enrollment	“Please, be reminded to take your blood pressure-lowering drug(s): <DRUG NAME & STRENGHT>: <DOSAGE>, <FREQUENCY>, <FURTHER INSTRUCTIONS, IF APPLICABLE>. Thank you very much for taking care of your health. Your SPPA trial research team.”
End-of-trial SMS	3 months after the enrolment	“Thank you very much for your participation in the SPPA trial. Your prescheduled appointment at the trial pharmacy is on < DATE>, please bring your marked drug package(s) with you. We will be looking forward to your visit. Your SPPA trial research team.”

#### Intervention group

Participants in the intervention group will receive sPhC provided by the trial pharmacist, the welcome SMS, and the end-of-trial SMS. Additionally, they will be receiving the investigated intervention, daily SMS reminders of antihypertensive medication intake, for three months. Behavioral perspective of the content and the framing of SMS reminders are not yet sufficiently understood [69]; therefore, we will focus on simple information provision according to the national and international pharmaceutical regulations and guidelines [53, 54, 67, 68]. The content of the SMS reminders will be personalized for each participant in terms of drug name, strength, dosage, frequency, and other applicable specifications. Complying with the pragmatic design of the trial, the SMS reminder structure follows information provided during the usual drug dispensation and counseling process as laid down by the Slovak national decree No. 129/2012 [67]. Thus, most of the information are available on the prescription and all of the collected data are already a well-established and required part of the sPhC in Slovakia. Furthermore, simple structure of the SMS reminder allows for future reproducibility. Table 1 shows the content of sample SMS reminders.

Delivery times will be customized to patients’ individual preferences. We have chosen the length of the intervention to be three months for two main reasons. First, previous studies have confirmed that a three-month period is sufficient to detect a significant change in medication adherence [70–72]. Second, according to Slovak law [68], chronic patients can receive their medication for a maximum of three months. Afterwards, they attend a regular medical visit, receive a new prescription, and thus visit the pharmacy usually in three months cycles. We believe this will increase the retention rate. For dissemination and coordination of the SMS reminders we will use FrontlineSMS, open access software, and a local operator Subscriber Identification Module Card. An external unblinded trial pharmacist will create, schedule, and send the SMS reminders according to the case report forms. The external unblinded trial pharmacist will have direct contact with neither the trial participants nor the trial pharmacists.

### Patient recruitment

Participants will be recruited in trial pharmacies while filling their prescriptions. Trial pharmacists will screen patients according to their prescription information (age, diagnosis, and medication). If deemed eligible, they will inform the patients about the SPPA trial and their potential participation.

Trial pharmacies will be selected according to their recruitment potential (number of hypertensive patients visiting the pharmacy per month). In case a center will not be able to reach the predefined enrolment target, an additional trial center, comparable in region characteristics, will be trained and initiated to complete the enrolment.

### Randomization, allocation, and concealment

Participants will be randomly assigned to either control or intervention group with a 1:1 allocation ratio. The external unblinded trial pharmacist will generate a simple randomization and allocation list with randomization numbers (patient trial codes) stratified by gender for each trial center. Freely available online software, Research Randomizer, will be used for this purpose [73]. The external unblinded trial pharmacist will provide each trial pharmacy with equal number of sequentially numbered, opaque, sealed randomization envelopes for male (blue) and female participants (red). Trial pharmacists will recruit patients in the natural, unpredictable order as they enter the pharmacy and agree to participate in the trial. After signing the informed consent form, trial pharmacists will assign a patient trial code to each participant from a randomization envelope selected in ascending order.

### Blinding

Due to the nature of the trial, it is not possible for the patients to be blinded. Trial pharmacists will inform the participants about the purpose of the trial and their random allocation to either receiving daily SMS reminders or not and will ask them not to disclose their allocation to the trial pharmacist or research team until the end of their follow-up visit. Trial pharmacists, performing blood pressure measurements, pill count calculations, and completing the MMAS-8 questionnaires with the participants (the assessors), will be blinded to the allocation of the intervention. The statistician will receive the final anonymized data after the end of trial and database lock. The project leader is the main contact person for trial participants in case of potential problems. Thus, it is possible that during these contacts patient allocation may be disclosed. However, since the project leader is involved neither in the assessment of the trial outcomes nor in the final statistical analysis, this potential partial unblinding will have no impact on the trial results. Other research members are blinded to the intervention allocation.

### Data collection, handling, and monitoring

Trial data will be collected at Visit 1 (day of patient enrolment) and at Visit 2 (follow-up visit after three months). Table 2 provides and overview of all case report forms that will be used in the trial for data collection. Furthermore, we will actively seek and collect signals of adverse events associated with antihypertensive medication intake reported by the participants. We will also collect anonymous reasons for participation refusal and discontinuation of participation. All trial forms and materials constituting the Appendixes of the SPPA trial protocol are available in Additional file 3.

**Table 2 Tab2:** Overview of Case Report Forms in the SPPA trial

Case Report Form/Questionnaire	Details	Time Point
Case Report Form Visit 1 – PART A	Antihypertensive medication specification Mobile phone number for SMS reminders Preferred time of SMS reminder	Visit 1
Case Report Form Visit 1 – PART B	Blood pressure measurement	Visit 1
Case Report Form Visit 1 – PART C	Medication adherence measurement via MMAS-8	Visit 1
Case Report Form Visit 1 – PART D	Patient information (Sociodemographic and health information, information on mobile phone usage)	Visit 1
Case Report Form Visit 2 – PART A	Medication adherence measurement via pill count	Visit 2
Case Report Form Visit 2 – PART B	Blood pressure measurement	Visit 2
Case Report Form Visit 2 – PART C	Medication adherence measurement via MMAS-8	Visit 2

During the recruitment period, the trial pharmacist will send password-protected scans of the Case Report Form Visit 1 – PART A and the Screening and Enrollment Log to the project leader via e-mail. The project leader will then forward the antihypertensive medication specification, mobile phone number, and preferred time for SMS reminder in a password-protected document to the external unblinded trial pharmacist via e-mail. Trial pharmacists will send copies of all trial forms, except Case Report Form Visit 1 – PART A, in sealed envelopes via recorded delivery to the research office located at Faculty of Pharmacy, Comenius University in Bratislava on a monthly basis. A separate data management team, whose members are not part of the research team, will enter the data into the pre-prepared, password-protected Microsoft Access Database. Two members of the data management team will do the data entry on a double-entry basis independently to ensure excellent quality of the data. Figure 1 depicts all trial data procedures and data workflow.

